#### Tai Chi group

The simplified 24-style Tai Chi will be used as a second intervention exercise as it is concise and easy to master by novices while retaining the core essentials of traditional Tai Chi. It consists of 24 movements, such as “starting momentum”, “wild horse mane”, and “white crane wings”, with a drill duration of about 8–10 min, and a total session duration of about 30 min including warm-up, practice, and the closing posture of Tai Chi. Training will be delivered 3 times per week at 17:00–18:30 both for convenience and temporal consistency with the other interventions. Each training session will be divided into three phases: a 5-min warm-up (including neck rotation, joint movement, lunge leg press), 20-min Tai Chi routine practice (including two repetitions), and the 5-min closing (pranayama relaxation, tapping the meridians). The selected Tai Chi training intensity aims for “slight sweating, steady breathing, and consistent movements”, and will be monitored by the Subjective Fatigue Scale (RPE), which requires the participants to maintain an RPE score of 11–13 (slightly tired but sustainable) during the training. At the same time, participants will use a wearable device to ensure that average heart rate remains at 50–65% of HRmax. The Tai Chi intervention will adopt “online + offline” dual supervision. During offline training, the coach will observe the participants' movements on video submitted via an online video application, from which the coach will provide remote guidance. Attendance will be summarized monthly. Compliance is defined as an attendance rate ≥80% (≥9 sessions completed over 4 weeks); if attendance is < 80%, reasons will be documented and participants will be encouraged to improve, with reasons recorded for sensitivity analysis.

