## Methods/design

### Study setting

This parallel randomized controlled clinical trial will be conducted at Third Affiliated Hospital of Henan University of Chinese Medicine, Henan Province, China, according to the principles outlined in Consolidated Standards of Reporting Trials (CONSORT), Standards for Reporting Interventions in Acupuncture Clinical Trials (STRICTA), and Standard Protocol Items: recommendations for Interventional Trials (SPIRIT) guidelines (Figure 1). Ninety full-time college students will be randomly and equally assigned to acupuncture, running, and Tai Chi groups. The allocated intervention will be conducted for 30 min, 3 times per week on alternating weekdays for a total of 4 weeks (w). The General Procrastination Scale (GPS) will be used as the primary outcome measure, with the Procrastination Assessment Scale for Students (PASS) and Physical Activity Rating Scale 3 (PARS-3) used as secondary outcome measures. Outcome measures will be conducted at baseline (0 w) and after 2 and 4 weeks of intervention. In addition, P300 and N200 will be measured by scalp EEG during the Go/No-go Emotion Detection task and Task Initiation Delay Paradigm (TIDP) to observe the effects of these interventions on cognitive control and error detection abilities.

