#### Running group

The running group will perform moderate-intensity continuous training (MICT) according to American College of Sports Medicine (ACSM) guidelines with precise exercise intensity control according to heart rate reserve (HRR) calculations. Maximum heart rate (HRmax) and anaerobic threshold heart rate (ATHR) will be measured for each participant at baseline using a standard treadmill escalating load test (Bruce protocol), and HRR calculated as HRR = HRmax-Resting Heart Rate (RHR). Training intensity will be maintained in the 60–75% HRR range (equivalent to 70–85% of maximum heart rate) by real-time monitoring using a wearable heart rate monitor. Participants will run 3 times per week for 30 min, including 5 min of brisk warm-up walking (heart rate controlled at 40–50% of HRR), 20 min of target intensity running, and 5 min of cold walking and dynamic stretching. The training time will be fixed at 17:00–18:30 every day to reduce the impacts of circadian factors. The dual-track “check-in + sports data upload” system will be used to supervise the activity, and participants will wear sports bracelets to record running distance, pace, and heart rate data. These data will be submitted weekly. Compliance is defined as an attendance rate ≥80% (≥9 sessions completed over 4 weeks). Participants with attendance < 80% will not be excluded from the intention-to-treat (ITT) analysis but will be excluded from the per-protocol (PP) analysis.

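### A monthly attendance summary in the 4-week Tai Chi programme may leave the step to encourage poor attenders with no sessions to act on

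*Protocol article*

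**What the plan says.** The Study setting section of the protocol article sets each intervention at "3 times per week on alternating weekdays for a total of 4 weeks". The Tai Chi group section repeats the frequency: "Training will be delivered 3 times per week at 17:00–18:30". That section then makes three statements in close succession:

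- On the interval: "Attendance will be summarized monthly".
- On the threshold: "Compliance is defined as an attendance rate ≥80% (≥9 sessions completed over 4 weeks".
- On the action: "if attendance is < 80%, reasons will be documented and participants will be encouraged to improve, with reasons recorded for sensitivity analysis".

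The Tai Chi section also describes online and offline supervision in which a coach looks at submitted videos and gives remote guidance. It gives no interval for that review.

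The Running group section describes a check-in and upload system with bracelets that record distance, pace and heart rate, and says "These data will be submitted weekly". It states the same compliance threshold but no review of attendance and no encouragement step. The Acupuncture group section gives the threshold with neither a reporting interval nor an encouragement step.

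The Data analysis section uses adherence twice, both times as a sensitivity analysis: a per-protocol analysis restricted to adherence of at least 80%, and a model with the number of completed sessions as a covariate.

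**The concern.** A step meant to improve attendance can only work while sessions remain. Here it stands beside a reporting interval about as long as the whole programme. The threshold is also defined over the full 4 weeks, and no interim value is given at which staff would act. Read together, the sentences describe a prompt that may first become due when nothing is left to attend.

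What is at stake is adherence in the Tai Chi arm and, through it, the two sensitivity analyses that depend on attendance. If absences that could have been corrected go unnoticed, fewer Tai Chi participants enter the per-protocol set and the completed-session counts are lower than they need have been. The documents give no figure from which the size of that loss could be estimated.

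**Working it through.** **Inputs.** Three sessions a week for 4 weeks (Study setting; Tai Chi group). Compliance at 80% or more, glossed as 9 or more sessions (Tai Chi group; the same gloss stands in the Acupuncture group and Running group sections). Summary interval monthly, with the start of the month not defined (Tai Chi group). Assumption: alternating weekdays means Monday, Wednesday and Friday.

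**Step 1, the plan's own threshold.** Sessions = 3 × 4 = 12. 80% of 12 = 0.80 × 12 = 9.6, so a rate of at least 80% takes 10 sessions (10/12 = 83.3%). Nine sessions is 9/12 = 75.0%. The two halves of the definition do not agree: a participant with exactly 9 sessions complies by count and does not comply by rate.

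**Step 2, day of the last session.** Counting the first session as day 1:

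| First session on | Day of session 12 |
|---|---|
| Monday | 26 |
| Wednesday | 27 |
| Friday | 27 |

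**Step 3, month counted from the participant's start.** A month is 28 to 31 days. The summary comes after day 26 or 27 in every case, so the sessions remaining are 12 − 12 = 0.

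**Step 4, calendar month.** All 313 Monday, Wednesday and Friday start dates in 2025 and 2026 were taken, and the sessions falling after the end of the starting month were counted.

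- No session left: 49/313 = 15.7%.
- At least one session left: 264/313 = 84.3%.
- Mean number left, counting zeros: about 5.1 of 12.

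On this reading the step can often act, but whether it can, and on how many sessions, is decided by the date of enrolment.

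**Step 5, weekly summary.** Sessions remaining after week w = 12 − 3w.

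| After week | After session | Sessions left |
|---|---|---|
| 1 | 3 | 9 |
| 2 | 6 | 6 |
| 3 | 9 | 3 |
| 4 | 12 | 0 |

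The step could then act three times before the last session.

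**Step 6, why the threshold matters to the trigger.** A participant who misses two sessions in week 1 can still reach 10/12 = 83.3%, which complies on either definition. One who misses all three can reach at most 9/12 = 75.0%, which complies by count but not by rate. Whether a prompt after week 1 can still bring that participant to compliance depends on how the definition is reconciled.

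**The case against.** The strongest reply is that the text does not make the monthly summary the only trigger. The clause on attendance below 80% follows the compliance definition and is not expressly tied to the summary. A coach who receives videos could notice missing ones at any time, and the calendar-month reading leaves sessions in hand for most start dates. This stands, and it is why the conclusion is that the step may have nothing left to act on, not that it cannot act. It does not remove the point. The video review is described as observing movements, has no stated interval and is not linked to attendance. The calendar-month reading makes the step depend on the enrolment date.

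It can also be said that reminder procedures belong in an operations manual and that an article condenses them. That would answer a complaint about missing detail. Here the interval and the step are both stated, and they fit each other poorly.

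A reader might infer that running attendance is checked four times for each Tai Chi check, and that a difference between those arms would partly reflect monitoring. The documents do not support this. What is weekly in the running arm is submission of bracelet data. Sessions run could be inferred from it, but no attendance review or reminder is stated there, and Tai Chi is the only arm with an encouragement step at all. The Tai Chi section also has its own monitoring of intensity, by perceived exertion and wearable heart rate, so an attendance interval is not a measure of how often dose is monitored.

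**Conclusion.** The point holds in a limited form. The stated interval fits badly with the stated step: counted from each participant's start, the only scheduled summary leaves 0 of 12 sessions; counted by calendar month, about 16% of start dates leave none and the rest leave a number set by chance. These figures rest on a Monday/Wednesday/Friday pattern with no rescheduled sessions and, for the calendar-month share, on start dates spread evenly over 2025 and 2026.

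The effect falls on adherence and on the per-protocol and adherence-covariate sensitivity analyses. The primary mixed model under intention-to-treat remains a valid comparison of the programmes as delivered, and no between-arm bias has been shown. The point is modest, but it is worth correcting because the remedy is nearly free and helps only if in place before participants start.

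Separately, the 80% and 9-session thresholds contradict each other in all three intervention sections. They must be reconciled before any trigger based on them can be applied.

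**What to change.** - In the Tai Chi group section, replace the monthly summary with a weekly attendance summary, and trigger the existing document-and-encourage step from the summaries after sessions 3, 6 and 9.
- State how attendance below the threshold is judged part-way through, for example sessions attended out of those scheduled so far.
- Put the same interval and the same step in the Acupuncture group and Running group sections, which state neither an attendance review nor an encouragement step.
- Reconcile the 80% and 9-session thresholds in all three sections, and carry the result into the per-protocol definition in Data analysis.

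The cost is a change of wording and a weekly look at attendance records that the compliance definition already requires. It adds no participants or visits, and the interventions themselves stay as they are.

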### Measurement of event-related potentials by EEG

A total of 120 participants will be recruited, including 90 with high levels of procrastination to be allocated randomly and equally to acupuncture, running, and Tai Chi groups, and a healthy control group (n = 30). All members of the research team received systematic training in EEG data acquisition and analysis, and participated in the full workflow of the pilot study, including data collection and pre-processing. EEG data will be recorded using a 32-channel actiCHamp Plus system (Brain Products, Germany). Electrodes will be placed according to the international 10–20 system, with bilateral mastoids serving as reference electrode points. Electrode impedances will be maintained below 5 kΩ, and signals will be sampled at 500 Hz. Online filtering will include a high-pass filter (0.1–0.5 Hz), a low-pass filter (30–50 Hz), and a 50 Hz notch filter to eliminate line noise. Data analyses will focus on midline frontal (Fz), central (Cz), parietal (Pz), and lateral frontal (F3, F4) electrodes. Pre-processing procedures, including filtering, artifact rejection, and independent component analysis (ICA), will be performed using MATLAB R2020b and EEGLAB v2019.0.

#### Experimental paradigms

##### Go/no-go emotional detection task

The Go/No-go emotional detection paradigm will be used to assess participants' emotional attentional bias and cognitive control. Stimuli will consist of 50 pictures, distributed equally across five emotional categories: anger, fear, happiness, sadness, and neutral (10 images per category). Stimuli will be presented in five pseudo-randomized blocks to avoid consecutive repetition of the same emotional category. In the task design, Go trials (25%) will only involve neutral images; participants will be required to respond quickly and accurately by pressing the spacebar when a neutral image is presented. No-go trials (75%) will only involve emotional images (depicting anger, fear, happiness, or sadness) and require participants to withhold all responses (no neutral images will be included in No-go trials). Each trial will begin with a central fixation cross (“+”), which will remain until stable fixation is established. The fixation cross will then be replaced by a stimulus (either emotional or neutral) presented for 150 ms, followed by a variable inter-stimulus interval (ISI) of 0–500 ms. Before the formal task, participants will complete 10–15 practice trials to ensure understanding of task requirements.

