The N200 ERP component usually appearing 160–240 ms after the presentation of a stimulus is primarily reflective of early attentional and cognitive processing, especially attentional allocation, and changes in N200 latency and amplitude are closely related to response inhibition and other aspects of cognitive control over behavior. Abnormalities in N200 among high procrastinators suggest a reduced ability to monitor task conflicts, making it difficult for these individuals to suppress distracting stimuli or prioritize tasks with perceived low short-term value (but possible higher delayed value) (47–49). One study reported a significant difference in N200 between the high and low procrastination groups as well as significant right lateralization of the visual ERP N1 among low procrastination individuals compared to the high procrastination group, suggesting that lower-level procrastinators are more alert to early information processing, while high procrastinators devote less attentional resources to tasks and show more impulsiveness and less control over immediate events (12). Patients with attention deficit hyperactivity disorder (ADHD) have also demonstrated a prolonged N200 latency, reflecting an inadequate allocation of attentional resources, and procrastination overlaps symptomatically with ADHD (including difficulty initiating tasks). Moreover, it is speculated that abnormalities in N200 may reflect similar underlying neural mechanisms (50, 51).

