## Discussion

The proposed study aims to evaluate the potential therapeutic effects of acupuncture and exercise (running and Tai Chi) on procrastination among college students and to elucidate the underlying cognitive mechanisms. Procrastination is a complex behavioral disorder involving multiple neural networks regulating self-control, emotion, and motivation by reward. The study design fully considers the multidimensional neural mechanisms of procrastination by measuring electrophysiological biomarkers reflecting cognitive control, attention sharing, and error detection ability (such as the ERPs P300 and N200) in addition to psychometric scale scores. It is anticipated that these multimodal measurements will provide a more comprehensive understanding of the neural mechanisms underlying procrastination, identify the most appropriate evidence-based interventions, and reveal potential biomarkers for future mechanistic and clinical investigation.

Acupuncture and exercise have numerous advantages as non-pharmacological interventions for neuromodulation and physiological regulation, respectively. Acupuncture may improve procrastination behavior by modulating brain self-control networks (including the dlPFC and ACC) and emotion regulation networks (involving the insula and OFC), while exercise may further enhance the effects of acupuncture-induced neuromodulation by promoting neuroplasticity and improving emotional regulation. The study design provides a comprehensive framework for exploring the efficacy of different interventions (acupuncture vs. running and Tai Chi) and a foundation for future studies testing combined interventions for the non-pharmaceutical treatment of procrastination.

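### Go is the minority response in the Go/No-go task, so an N200 change does not securely show better inhibition, and the promised error-detection effect has no error measure behind it

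*Protocol article*

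**What the plan says.** All places are in the protocol article.

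- **Task proportions** (Go/no-go emotional detection task): "Go trials (25%) will only involve neutral images" and "No-go trials (75%) will only involve emotional images".
- **Picture set** (same section): "Stimuli will consist of 50 pictures, distributed equally across five emotional categories", listed as "anger, fear, happiness, sadness, and neutral (10 images per category"). That is 10 neutral and 40 emotional pictures. There are five blocks, ordered so that one category does not follow itself. The article gives neither the number of trials nor the number of showings per picture.
- **Purpose of the task** (same section): emotional attentional bias and cognitive control.
- **What the ERPs should show** (Study setting, and similarly the Abstract): P300 and N200 are recorded in this task and in the Task Initiation Delay Paradigm (TIDP) "to observe the effects of these interventions on cognitive control and error detection abilities". The Discussion describes the design as "measuring electrophysiological biomarkers reflecting cognitive control, attention sharing, and error detection ability (such as the ERPs P300 and N200").
- **How N200 is understood** (Introduction): it appears 160–240 ms after a stimulus, and "changes in N200 latency and amplitude are closely related to response inhibition and other aspects of cognitive control over behavior". Abnormal N200 in high procrastinators is linked there to weaker monitoring of task conflict.
- **Predictions** (Expected results): N200 amplitude should rise toward the healthy-control level after treatment. P300 changes are read as less emotional bias and more task focus, and in the TIDP as lower cognitive load on 2,000 ms delays.

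**The concern.** A No-go trial tests inhibition to the extent that the participant is inclined to press. Here withholding is the correct action on three quarters of trials or more, so the inclination to press is weak and the task works largely as detection of an infrequent target. If N200 rises after treatment, the Introduction's account invites the conclusion that inhibition or conflict monitoring improved. Better detection of rare neutral pictures would explain the same rise.

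Error detection is a second matter. It is promised in three places, but the only components named are P300 and N200, and the article times N200 from the stimulus. Nothing that depends on an error being made is listed as a measure.

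The neurocognitive mechanism is a stated objective, and Expected results puts these ERPs forward as objective markers of whether the interventions work. The construct attached to them therefore decides what the trial can claim. Task proportions cannot be changed once recordings exist.

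**Working it through.** **1. The Go share.** Inputs: 10 neutral and 40 emotional pictures; neutral is always Go.

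- Equal showing: 10/50 = 20%, which does not reproduce the stated 25%.
- One pass through the set: 25% of 50 = 12.5 trials. One pass in each of five blocks (assumed): 25% of 250 = 62.5 trials. Neither is a whole number.
- Unequal showing, with each neutral picture shown *a* times and each emotional picture *b* times: 10a/(10a + 40b) = 0.25, so 30a = 40b and a/b = 4/3. The smallest case is 40 neutral + 120 emotional = 160 trials, and 40/160 = 25%.

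So 25% is attainable, but only with a 4:3 repetition that the text does not state. On either reading Go is the minority response.

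**2. The tendency to press.** Neutral is one of the five listed categories, so under the order rule no Go trial follows another. Each Go can then precede at most one No-go. With Go share *g*, the share of No-go trials directly preceded by a Go is at most g/(1 − g):

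- g = 0.20: 0.20/0.80 = 25%
- g = 0.25: 0.25/0.75 = 33%

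No run of presses can build up before a No-go picture.

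**3. Error detection, promise against measure.**

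| Place | Content |
|---|---|
| Abstract, Study setting | effects on error detection from P300/N200, both tasks |
| Discussion | P300/N200 as markers of error detection ability |
| Go/no-go section | no error rate or response-locked component |
| TIDP section | purpose is readiness to start and perception of delay; no error measure |
| Expected results | no prediction about errors in either task |

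This comparison needs no assumed figure.

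**4. Would there be enough errors to analyse?** Expected commission errors per person per session = No-go trials × error rate. The article gives neither input, so all values below are assumptions.

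| Trials (No-go) | 1% | 2% | 5% | 10% |
|---|---|---|---|---|
| 50 (40) | 0.4 | 0.8 | 2.0 | 4.0 |
| 160 (120) | 1.2 | 2.4 | 6.0 | 12.0 |
| 250 (200) | 2.0 | 4.0 | 10.0 | 20.0 |

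Errors are scarce if the task is short or the rate low, but not in a long task at 5–10%. The article does not settle which applies.

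**The case against.** The case for the plan has real strength.

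- **Some press tendency exists.** Participants must respond quickly, pictures last 150 ms and the interval after them is 0–500 ms. This stands: the tendency is weak, not absent.
- **Inhibition is not the declared aim.** The task section names attentional bias and cognitive control, and the Introduction describes N200 first of all as attentional allocation, which rare-target detection can engage. Expected results does not mention inhibition. This also stands. It limits the point to the inhibition and conflict-monitoring reading of N200 and leaves the P300 bias predictions alone.
- **The TIDP shares the error-detection aim.** It is a speeded two-choice task in which errors can occur. True, but the article names no error measure there either, so the gap remains.
- **An article condenses.** Trial totals may well be in a fuller document. That excuses the missing count. It does not excuse printing two proportions that disagree under equal showing, or attributing error detection to components for which no error-based analysis is described.
- **The damage is bounded.** Data analysis calls the ERP work exploratory, and every randomised arm performs the same task, so comparisons between arms are not biased by this. That stands: what is at risk is the label put on a difference.

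**Conclusion.** The point holds in a limited form. Go is the minority response (25% or 20%), and two Go trials do not follow each other if neutral counts as a category under the order rule. The inhibition or conflict-monitoring reading of an N200 change is therefore not secured against simple target detection. The error-detection claim has no stated measure in either task. The 20% figure assumes equal showing of pictures. The judgement that pressing is only weakly prepared rests on task-design reasoning, not on a figure in the article.

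A reader might infer more, and the article does not support it:

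- *That there is no response to inhibit, or that nothing about inhibition can be learned.* The speeded instruction leaves some tendency to press, and no figure in the article shows otherwise.
- *That errors will be too few.* This depends on a trial count and an error rate that are not given; the assumed range runs from 0.4 to 20 per person per session.
- *That 25% is simply wrong.* A 4:3 repetition yields it exactly.
- *That the cure is to make Go 75% of trials.* As a change of ratio alone it breaks other parts of the design (see the fix).

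The consequence falls on the mechanistic objective. The GPS primary outcome, the sample size and the P300 attentional-bias predictions are untouched.

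**What to change.** 1. **Error detection.** Either define an error measure from data already recorded, or delete the error-detection wording from the Abstract, Study setting and Discussion. The measure would be the commission or choice error rate in both tasks, plus a response-locked error negativity at Fz/Cz with a minimum error count set in advance. Deleting costs nothing. Adding costs a little analysis, and some participants may have too few errors for the error negativity.
2. **Interpretation.** State that N200 and P300 in the Go/No-go task will be read as target detection, attentional allocation and emotional attention, not response inhibition. The cost is a narrower mechanistic claim.
3. **Proportions.** Either state 20%/80% with every picture shown equally often, or keep 25%/75% and state the 4:3 repetition and the trial total. The second option makes each Go picture slightly more familiar than each No-go picture.

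If an inhibition claim is wanted, redesign the task as a whole, including picture set and order rule. Raising neutral Go to 75% with the present pictures would show each neutral picture (75/10)/(25/40) = 12 times as often as each emotional one. It could not satisfy the rule against repeating a category. It would also cut negative-emotion trials (three of the four emotional categories) from 75% × 3/4 ≈ 56% to 25% × 3/4 ≈ 19% of the task, and the P300 hypothesis depends on those trials.
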